### 2.12. Definition of Population

The primary analysis is carried out on the per-protocol set (PP) as usual in non-inferiority studies. Sensitivity analyses with the intention-to-treat (ITT) population and the as-treated (AT) population will be carried out and any differences will be discussed.

### 2.13. Statistical Analysis

A statistical analysis plan with more technical details on the methods used will be written prior to database lock.

#### 2.13.1. Primary Endpoint

The sensitivity and specificity of the transcranial and direct cortical stimulation with regard to motor deficit at discharge or 7 days after the operation are calculated and compared between the procedures using the Farrington-Manning test. Sensitivity refers to the probability of having a motor deficit at discharge (or 7 days after surgery), after reaching a predefined deterioration of MEP according to the applied alarm criterion during tumor resection. Specificity refers to the probability of not having a motor deficit at discharge (or 7 days after surgery) while not reaching a predefined deterioration of MEP according to the applied alarm criterion during tumor resection. The sensitivity is tested for superiority to a two-sided significance level of 5%; the specificity is tested for non-inferiority with a non-inferiority threshold of 10% with a one-sided significance level of 2.5%. One method is superior to another if it has been possible to demonstrate superiority in sensitivity and non-inferiority in specificity (intersection hypothesis). A correction of control of the type I error is, therefore, not necessary. Despite the conservative design, the main aim of the study is to gain a first understanding of the underlying differences in prognostic sensitivity and specificity between the two procedures.

#### 2.13.2. Secondary Endpoints

The secondary endpoint, extent of resection, is analyzed between the randomization groups using an ANCOVA (Analysis of Covariance) with baseline tumor mass as a covariate. The proportion of patients with and without motor deficit is compared between the randomization groups using the chi-square test. Differences in the Barthel Index and in the Karnofsky Performance Score at discharge and after 3 months as well as in EORTC QOL C30 and BDI-S after 3 months are analyzed using an ANCOVA.

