## Abstract

Background: Monitoring of motor function during surgery for supratentorial tumors under general anesthesia applies either transcranial electrical stimulation (TES) or direct cortical stimulation (DCS) to elicit motor-evoked potentials. To date, there is no guideline that favor one method over the other. Therefore, we designed this randomized study to compare between both methods regarding the prediction of postoperative motor deficits and extent of tumor resection. Methods: This is a multicenter (six centers in Germany and one in Switzerland), double blind, parallel group, exploratory, randomized controlled clinical trial. Patients without or with mild paresis, who are scheduled for surgical resection of motor-eloquent brain tumors under general anesthesia will be randomized to surgical resection under TES or surgical resection under DCS. The primary endpoint is sensitivity and specificity in prognosis of motor function 7 days after surgery. The main secondary endpoint is the extent of tumor resection. The study is planned to include 120 patients within 2 years. Discussion: The present exploratory study should compare TES and DCS regarding sensitivity and specificity in predicting postoperative motor deficit and extent of tumor resection to calculate the required number of patients in a confirmatory trial to test the superiority of one method over the other.

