#### 2.8.2. Main Secondary Outcome Measure

Proportion of remaining tumor will be measured based on pre- and postoperative MRI. Preoperative MRI is performed within 1–2 weeks prior to surgery and postoperative MRT is performed within 72 h after surgery. Thin slice sagittal magnetic resonance T1 contrast imaging in case of enhancing tumors and T2 flair images (minimum 160 slices) are transferred into iPlan 3.0 cranial (BrainLab, Munich, Germany). This software enables a semiautomatic object drawing using the object creation tool. To measure the tumor volume, its area is encircled in each slice with manual correction if required. Afterwards, the tumor volume expressed in ccm, is extracted using the advanced manipulation function. The measurement is performed independently by a neurosurgeon and a neuroradiologist.

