### 2.9. Methods against Bias

Selection bias is minimized by randomizing patients, stratified by center, tumor localization and contrast medium enhancement (1:1 treatment ratio). Block randomization with random block length will be performed. Performance bias is reduced by the double-blind study design. Neither the patient nor the neurosurgeon will be aware of the applied warning criteria. Detection bias is reduced by blinding outcome assessors to the data until the end of the study. A statistical analysis plan (SAP) will be written prior to database lock and all results will be published independently of specific findings to minimize reporting bias.

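### The stated analyses of extent of resection and motor deficit do not use the factors that stratify randomization; if those factors are prognostic, the tests are conservative and the resection comparison loses precision

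*Protocol article*

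**What the plan says.** Protocol section 2.9 describes allocation as "stratified by center, tumor localization and contrast medium enhancement (1:1 treatment ratio"), in blocks of random length. The Abstract gives the centers as "six centers in Germany and one in Switzerland", seven in all.

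Section 2.13.2 then sets out the comparisons between arms:

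- Extent of resection "is analyzed between the randomization groups using an ANCOVA (Analysis of Covariance) with baseline tumor mass as a covariate". No other covariate is named.
- For the deficit rate: "The proportion of patients with and without motor deficit is compared between the randomization groups using the chi-square test".
- Barthel and Karnofsky scores, and differences "in EORTC QOL C30 and BDI-S after 3 months are analyzed using an ANCOVA". No covariate is named for any of these.

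Section 2.13 defers technical detail to an SAP, still to be written before database lock, which is not shown.

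**The concern.** Stratified randomization makes the arms similar on the stratification factors. The treatment difference therefore varies less from one possible allocation to another than it would under simple randomization. An analysis that leaves the factors out keeps their variance in its error term and does not credit that reduction. If the factors predict the outcome, the standard error is too large, the test rejects less often than its nominal level, and the interval is wider than it need be.

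This matters most for extent of resection, which section 2.8.2 makes the main secondary outcome. Section 2.2 lists the effect of modality on resection and on postoperative paresis among the trial's aims. Both are direct comparisons of the arms as randomized. The trial is meant to inform a later confirmatory study, so an overstated error variance for resection could be carried into any planning based on it.

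There are grounds in the document to think the factors could be prognostic. The sponsor chose them for stratification. Imaging for tumor volume also refers to enhancement: "Thin slice sagittal magnetic resonance T1 contrast imaging in case of enhancing tumors and T2 flair images". Section 2.7.1 leaves anesthesia to each center's local standard within common rules.

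**Working it through.** **The plan's own figure.** There is none to reproduce. Section 2.11 gives interval widths only for differences in sensitivity and specificity, not for resection or the deficit rate.

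**Inputs from the protocol.** Seven centers (Abstract); stratification by center, localization and enhancement, 1:1 (2.9); 110 evaluable patients and a 30% deficit rate (2.11); baseline tumor mass as the one named covariate, and an unstratified chi-square test (2.13.2).

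**Assumptions.** Localization and enhancement have two levels each, and block lengths are 2 or 4; the article gives neither. R² is the share of outcome variance explained by the three factors together, varied from 0 to 0.30. For resection it is the share left after baseline tumor mass. For motor deficit it applies to a latent continuous scale behind the yes/no outcome.

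**Step 1: sparsity.** 7 × 2 × 2 = 28 strata, and 110 / 28 ≈ 3.9 patients per stratum. Adjustment has to be by main effects: 6 + 1 + 1 = 8 extra parameters.

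**Step 2: resection, by formula.** Interval width adjusted / unadjusted ≈ √(1 − R²) × t(0.975; 99) / t(0.975; 107), where 107 = 110 − 3 and 99 = 107 − 8. Results: 1.001 at R² = 0, 0.976 at 0.05, 0.950 at 0.10, 0.895 at 0.20 and 0.837 at 0.30.

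**Step 3: simulation.** The formula ignores chance imbalance left over in incomplete blocks. 3,000 trials of 110 patients were therefore simulated for each R², with stratified permuted blocks and no true arm difference. Resection was analyzed by ANCOVA on baseline tumor mass, with and without the eight stratum terms. Motor deficit was analyzed by the plain chi-square test and unadjusted risk difference, and by a linear-model risk difference with the same eight terms. Resection widths are in residual standard deviations; deficit widths are in proportions.

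| R² | Resection width, unadjusted → adjusted | Ratio | Deficit width, unadjusted → adjusted | Ratio | Type I error, ANCOVA unadjusted / adjusted | Type I error, chi-square / adjusted |
|---|---|---|---|---|---|---|
| 0 | 0.758 → 0.765 | 1.009 | 0.339 → 0.349 | 1.029 | 5.5% / 5.4% | 5.2% / 5.0% |
| 0.05 | 0.758 → 0.745 | 0.983 | 0.340 → 0.344 | 1.014 | 4.1% / 4.5% | 4.9% / 5.3% |
| 0.10 | 0.760 → 0.726 | 0.956 | 0.340 → 0.339 | 0.999 | 4.3% / 5.2% | 4.6% / 4.9% |
| 0.20 | 0.760 → 0.685 | 0.902 | 0.340 → 0.328 | 0.965 | 3.5% / 5.2% | 4.0% / 5.3% |
| 0.30 | 0.759 → 0.640 | 0.843 | 0.340 → 0.317 | 0.931 | 2.3% / 4.8% | 3.4% / 5.2% |

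The simulation error of a 5% rate is √(0.05 × 0.95 / 3000) ≈ 0.4 percentage points. The falls to 2.3% and 3.4% are therefore real; the small differences at low R² are not informative.

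**Step 4: in patients.** For resection, the equivalent sample size is 1 / ratio²: 1 / 1.009² = 0.98 at R² = 0, 1 / 0.956² = 1.09 at 0.10 and 1 / 0.843² = 1.41 at 0.30.

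**Reading the deficit columns.** The adjusted interval uses t on 110 − 10 = 100 degrees of freedom and the unadjusted one uses 1.96. That alone contributes 1.984 / 1.960 = 1.012, so part of the 3% penalty at R² = 0 is a difference of convention.

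**The case against.** The strongest reply is that a journal article does not list every covariate. The SAP will hold the detail, and naming baseline tumor mass does not forbid further terms. That stands for the Barthel, Karnofsky, EORTC and BDI-S models, which name no covariate and are simply open. It stands less well for resection, where a method and one covariate are stated. It does not stand for motor deficit: a plain chi-square test has no place for strata, so an SAP that adjusted would depart from the stated method.

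A second reply is that the loss is assumed. This is correct. The documents give no R², and at small values the gain is negligible or slightly negative. Section 2.13.2 also plans a test for motor deficit and no interval, so what follows from the stated plan there is a conservative test.

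Third, these are secondary analyses in an exploratory trial, and the error is on the safe side. This stands and limits the weight of the point.

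A reader might go further in three ways that the documents do not support:

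- That no analysis in the trial adjusts for the strata. The open ANCOVAs and the unseen SAP rule out that statement. The primary comparison ("compared between the procedures using the Farrington-Manning test") also names no strata, but the sizes given here do not apply to it.
- That the imaging wording biases the resection comparison. The sentence does not clearly assign one sequence to each tumor type. The outcome is a proportion of each patient's own tumor, and stratification balances enhancement between arms.
- That adjustment is free. It uses eight degrees of freedom and can widen intervals slightly.

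**Conclusion.** The mismatch between sections 2.9 and 2.13.2 is real for extent of resection and motor deficit, and it is a minor efficiency point. There is no bias, and type I error is not inflated. If the strata are prognostic, the stated tests are conservative: at an assumed R² of 0.30, true type I error is about 2.3% for the ANCOVA and 3.4% for the chi-square test, against a nominal 5%.

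The case is stronger for resection, where the range runs from an interval about 1% wider to one about 16% narrower, so the possible gain is much larger than the possible loss. For motor deficit the range is from about 3% wider to about 7% narrower, and there is no gain until R² passes about 0.10. These sizes rest on the assumed R², two levels each for localization and enhancement, and 110 patients analyzed.

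**What to change.** In section 2.13.2 and the SAP:

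- **Extent of resection.** Keep baseline tumor mass and add tumor localization, contrast enhancement and center as main effects. Pool small centers by a rule fixed before unblinding, or fit center as a random effect. Do not cross the factors, given about four patients per stratum.
- **Motor deficit.** Replace the plain chi-square test with a stratified or adjusted comparison, for example a Mantel-Haenszel risk difference by localization and enhancement, reported with its interval. Staying on the risk-difference scale keeps the quantity the same as in an unadjusted comparison of proportions. This version leaves center out, so it recovers only the part of the gain due to the other two factors; the figures above are for all three.
- **Functional and quality-of-life ANCOVAs.** State their covariates in the SAP, preferably in line with the resection model.

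The cost is a few sentences, a few degrees of freedom, and intervals at most about 1% (resection) to 3% (motor deficit) wider if the factors turn out not to be prognostic. All three factors are already recorded for randomization, and the change can be made while the SAP is still to be written.

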### 2.14. Study Initiation

An on-site study initiation will be undertaken at each participating center. Details of the interventions including TES and DCS will be discussed thoroughly and demonstrated in practice using a standardized scenario that will be run on the device that is used for intraoperative monitoring. In addition, each participating study center receives a study-specific training on good clinical practice requirements.

### 2.15. Study Monitoring

The Clinical Trial Unit of the University medical center Göttingen applies a risk-based monitoring concept, which is described in a study-specific monitoring plan. The purpose of trial monitoring is to verify that:The rights and well-being of patients are protected.The reported trial data are accurate, complete, and verifiable from source documents.The conduct of the trial is in compliance with the currently approved protocol/amendment(s), with GCP, and with the applicable regulatory requirement(s).

### 2.16. Adverse Events

The applied methods for intraoperative monitoring are already well established in the clinical routine. We expect study-related adverse events to take place perioperatively at a very low rate and include epileptic seizures and lip and tongue injuries. These will be considered in the results and final analyses. In case of intraoperative seizures, all kinds of stimulations are stopped, and cold saline is applied on the exposed cortex along with intravenous application of Benzodiazepine or Thiopental if needed.

An interim analysis will take place after inclusion of 60 patients. It will evaluate the rate of postoperative paresis and the extent of tumor resection in comparison to the available literature.

### 2.17. Drop-Out Criteria and Termination of the Study

Withdrawal of patient’s consent, significant violation of the study protocol, cerebral ischemia, or intracerebral hemorrhage that occurs in the postoperative course and requires either a surgical intervention or an ICU-surveillance and is associated with a deterioration of the motor status are the main drop-out criteria. A violation of the study protocol is considered significant if it affects blinding or the interpretation of intraoperative monitoring.

The primary investigator will terminate the study when the interim analysis reveals a significantly higher rate of postoperative paresis or a lower extent of tumor resection than what has been reported in the literature. Major unexpected events can also lead to the termination of the study.

### 2.18. Data Management

Data will be entered remotely via an electronic case report form (eCRF) and stored in a provided SecuTrial^®^ database. SecuTrial^®^ is an established web solution facilitating the development of 21 CFR Part 11 conform web applications. Offsite data checks for plausibility and missing data will be performed during the complete course of the study to ensure high data quality and monitor recruitment. Inconsistent data will result in queries and/or planned visits for source data verification. After database deactivation, a copy of the database is password encrypted and archived for a 10-year period within the UMG. After publication of the primary results, all data/metadata will be anonymized and published in an open access repository (e.g., Publisso) in order to guarantee data access by third parties. To obtain long-term outcomes, including progression-free survival and overall survival, we plan to transfer the database to a prospective registry in a separate project.

## 3. Discussion

The presented trial is the first to address intraoperative neuromonitoring with TES and DCS-MEP during brain tumor resection under general anesthesia in a prospective randomized manner. Through its blinded design, the study is expected to demonstrate the true effect of each of the investigated monitoring methods on the motor status as a primary endpoint and on the extent of tumor resection as a secondary endpoint. There are several reports on intraoperative monitoring under general anesthesia with a large diversity regarding the stimulation modalities and the alarm criteria [15,16,17,18,19]. In general, one of two stimulation modalities are used to gain MEP, i.e., TES or DCS [6,20,21,22,23]. The reason to choose one method over the other has rarely been discussed. The inclusion criteria of the current trial define tumor localization that allows for an appropriate use of both methods. Patients with tumor infiltration of the precentral gyrus will not be included, because the craniotomy in these patients has to expose the primary motor cortex and, thus, prohibits a correct installation of the dermal electrodes needed for TES. Patients with severe preoperative paresis will also not be included, as this might be associated with an unsuccessful eliciting of intraoperative MEP.

Interpretation of changes in intraoperative MEP can be challenging. Available alarm criteria aim at preventing and predicting deterioration of postoperative motor function. An alarm criterion based on bilateral evaluation of motor threshold has been recently introduced for the evaluation of transcranial MEP during resection of supratentorial tumors [9]. In comparison to the conventional amplitude-based alarm criterion, the threshold criterion had a higher sensitivity and specificity in prediction of postoperative deterioration of motor function [10]. Therefore, it was chosen to be used in the study arm that applies TES during tumor resection. For DCS, both threshold- and amplitude-based alarm criteria were described with high sensitivity and specificity, and there is no study that compares these criteria during DCS. Therefore, a combination of both criteria was chosen to be used in the study arm that applies DCS during tumor resection.

The primary endpoint was set at discharge or one week after surgery, because this is the time point at which patient ability to undergo adjuvant therapy is evaluated. Motor status at the 3-month follow-up was not chosen as a primary but as a secondary endpoint, because many patients with brain tumors have to receive radio- and/or chemotherapy prior to this follow-up, which might be associated with a secondary deterioration of motor function, leading to evaluation bias. Using the Barthel index and Karnofsky index as secondary endpoints is necessary from our point of view, because both are strongly correlated to the motor function and used for evaluation of patient’s ability for further treatment or the need for rehabilitation or nursing facilities. All primary and secondary endpoints, including Barthel and Karnofsky indexes, are very significant measures for the quality of life and the ability to undergo treatment and influence the prognosis of patients with brain tumors. They have been validated and utilized as primary or secondary endpoint in clinical trials [24,25,26]. Self-reported quality of life using EORTC QOL C30 and BDI-S will enable us to gain concrete information about the effect of deterioration of motor function on the patient’s quality of life and their emotional health. These questionnaires have been validated in numerous papers addressing quality of life in cancer patients [27,28,29,30,31].

## 4. Conclusions

This trial was designed as an exploratory study to investigate sensitivity and specificity of TES and DCS in predicting postoperative motor deficits and study the influence of stimulation modality on the extent of tumor resection. The results of this trial will allow us to calculate the required number of patients in a confirmatory trial to test the superiority of one method over the other and will probably pave the way for a standardized evidence-based use of intraoperative monitoring during resection of supratentorial tumors. This will benefit patients suffering from brain tumors as well as neurosurgeon and neurophysiologist that are involved in the surgical treatment of brain tumors.

## Figures and Tables

**Figure 1 biomedicines-09-01490-f001:**
[figure not shown]
Trial flow diagram. MEP = motor-evoked potentials; TES-MEP = MEP after transcranial electrical stimulation; DCS-MEP = MEP after direct cortical stimulation.

## Data Availability

This manuscript is based on the most recent protocol version, version 3.0 October 2020.
